## Abstract

**Background:**

Irritable bowel syndrome (IBS) is a common gastrointestinal functional disorder with no effective therapy. Traditional Chinese medicine (TCM) is one of the most common complementary therapies in China. We designed this study to evaluate the efficacy and safety of *Shun-Qi-Tong-Xie* Granule (SQTX Granule), a TCM treatment, in patients with IBS with diarrhea (IBS-D).

**Methods/Design:**

A randomised, double-blinded, placebo-controlled, multi-centre, superiority clinical trial to evaluate the efficacy and safety of SQTX Granule is proposed. Eligible patients (Rome III) with IBD-S will be randomly assigned into SQTX Granule group and the placebo group. Patients will receive a 28-day treatment and a 2-month follow-up. The primary outcome measures include the scores of IBS-quality of life (IBS-QOL) rating scale and IBS-symptom severity scale (IBS-SSS) rating scale. The secondary outcome measures include the improvement of symptom scores, and the duration of abdominal pain and diarrhea.

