## Methods/design

### Design

This study is designed as a randomised, double-blinded, placebo-controlled, multi-centre, superiority clinical trial. This study is a phase III clinical trial and has been authorised by the CFDA (Approval Number 2007 L02218). In addition, the study is registered with the Chinese Clinical Trial Registry (ChiCTR-TRC-14004241). The study is financially supported by Shaanxi Bosen Biological Pharmaceutical Group Co. Ltd, Xi’an, China. This funding source is providing test drugs, but it had no role in the design of this study and does not have any responsibility for analyses, interpretation of the data or the decision to submit results. Trained research nurses introduce the trial to patients, and give them information sheets and consent forms. All patients have to give their written informed consent prior to enrolment. The study’s flow chart is shown in Figure 
1.

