### Sample size calculation

According to the results of Phase II clinical trial, the response rates of SQTX Granule and placebo were 0.51 and 0.33, respectively. Assuming the response rates for TCM and placebo were 0.5 and 0.35, the sample size was calculated under the setting of alpha = 0.05 and beta = 0.80. Taking into account a drop-out of 15%, the sample size needs to be 150 cases for each group. A total of 440 patients will be recruited in this trial, including 330 cases for the SQTX Granule group and 110 cases for the placebo group in a 3:1 ratio.

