### Outcome assessment

#### Primary outcome

• Scores of IBS-quality of life rating scale (IBS-QOL) rating scale
[21]

• Scores of IBS-symptom severity scale (IBS-SSS) rating scale
[22]

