### Data analysis

Statistical analysis will be conducted based on an intention-to-treat (ITT) principle. All subjects who were treated with at least one dose of the study drug and had at least one clinical observation after starting the treatment comprise FAS. All treated subjects without any major protocol deviations comprise PPS. The statistical analysis will be performed using the SAS 8.1 software (SAS, Cary, NC, USA). The statistical significance is defined as a two-sided *P*-value of < 0.05. Baseline differences among the groups will be assessed with the use of the one-factor analysis of variance or the Mann-Whitney *U-*test for measurement data and the χ^2^ test or the Wilcoxon test for enumeration data. For categorical variables, a χ^2^ test or Fisher’s exact test will be used. The changes from baseline to endpoint of treatment in scores will be assessed with the use of a paired *t*-test for measurement data and a signed rank test for enumeration data. Comparisons between groups will be conducted by using an analysis of variance (ANOVA) and a rank test.

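### Two primary outcomes share one two-sided 0.05 threshold with no success rule; if a win on either suffices, family-wise error is about 8–10%

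*Protocol article*

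**What the plan says.** The abstract and the body agree that there are two primary outcomes. The abstract states: "The primary outcome measures include the scores of IBS-quality of life (IBS-QOL) rating scale and IBS-symptom severity scale (IBS-SSS) rating scale". The Primary outcome section lists "Scores of IBS-quality of life rating scale (IBS-QOL) rating scale" and "Scores of IBS-symptom severity scale (IBS-SSS) rating scale" as two bullets of equal rank, with nothing to say which one decides the trial or whether both do.

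The Design section describes a "randomised, double-blinded, placebo-controlled, multi-centre, superiority clinical trial" and identifies it as phase III, so a claim of superiority is its purpose.

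The Data analysis section sets the only significance rule: "The statistical significance is defined as a two-sided *P*-value of < 0.05". For the treatment comparison it adds "Comparisons between groups will be conducted by using an analysis of variance (ANOVA) and a rank test". Neither sentence separates the primary scores from each other or from other variables.

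The Sample size calculation section gives "the sample size was calculated under the setting of alpha = 0.05 and beta = 0.80", applied to response rates of 0.5 and 0.35. A response rate is neither of the two primary scores, so this section does not imply a success rule either.

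**The concern.** A confirmatory trial needs to say in advance what result counts as success. With two primaries there are three possible outcomes: both scores significant, neither significant, or one of the two. The article settles the first two but not the third.

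Read as written, a significant result on either score meets the stated threshold and can be reported as superiority. Two chances at 0.05 give a false-positive probability above 0.05 for the trial as a whole. If the rule is chosen after the data are seen, a split result can be read as success or failure according to which score won, and no later analysis can restore control of the error rate.

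**Working it through.** **Plan's own figure.** The article states no family-wise error rate. The only figure to compare with is the 0.05 threshold itself.

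**Inputs from the article.** Two primary scores (Primary outcome); two-sided 0.05 for each test (Data analysis).

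**Assumptions.** One test per score, with test statistics Z1 and Z2 jointly normal under no treatment effect on either score, and correlation ρ between them. The article gives no ρ, so I show a range. The critical value is 1.96.

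**Step 1: independent scores.** P(at least one significant) = 1 − (1 − 0.05)² = 1 − 0.9025 = 0.0975.

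**Step 2: correlated scores, either suffices.** P(at least one significant) = 1 − P(|Z1| < 1.96 and |Z2| < 1.96), from the bivariate normal distribution.

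**Step 3: direction favouring the drug only.** With both scores oriented so that positive values favour the drug, P = 1 − P(Z1 < 1.96 and Z2 < 1.96). The nominal value for one test is 0.025.

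**Step 4: both required.** P(both significant) = 0.05 + 0.05 − P(at least one significant).

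| ρ (assumed) | Either suffices, two-sided | Either suffices, favouring drug | Both required, no effect on either score |
|---|---|---|---|
| 0 | 9.75% | 4.9% | 0.25% |
| 0.3 | 9.5% | 4.8% | 0.5% |
| 0.5 | 9.1% | 4.5% | 0.9% |
| 0.7 | 8.4% | 4.2% | 1.7% |
| 0.9 | 7.0% | 3.5% | 3.0% |

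The last column assumes no effect on either score. If the drug affects one score strongly and the other not at all, the error of a both-required rule approaches 5% but cannot exceed it, because the test of the unaffected score must itself reject.

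**Step 5: do the remedies hold 5%?** In a fixed sequence, a false claim when neither score is affected requires the first test to reject, so the error is 5%. For Holm, it requires the smaller P-value to fall below 0.025, so the error is 1 − 0.975² = 4.9% at ρ = 0 and 4.65% at ρ = 0.5. Requiring both is covered in Step 4.

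**The case against.** The strongest reply is that this is a condensed article. Testing order and multiplicity adjustment are often placed in the full protocol or the analysis plan, neither of which is shown, and the article nowhere says that one score suffices. This stands as a reason for caution: the rule may exist elsewhere. It does not dispose of the point. Which primary outcome or outcomes decide the trial is a design choice, and the article itself fixes two primaries, one unqualified 0.05 threshold and a superiority aim.

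A second reply is that the two-sided figure counts false wins for placebo. That is correct, and about half of it is of that kind. The relative inflation in the direction that matters is similar, 4.2–4.9% against 2.5% for correlations from 0.7 to 0.

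Two stronger readings are tempting, and the article supports neither:

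- A reader might infer that the trial's type I error exceeds 5% whatever rule is used. It does not if both scores are required, and the article leaves that possibility open.
- A reader might infer that requiring both scores falsifies a stated 80% power. The power figure (printed as a value of beta) belongs to a response rate. No power, effect size or standard deviation is given for IBS-QOL or IBS-SSS, so there is no stated power for the scores to contradict, and no basis for a joint-power figure.

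**Conclusion.** The concern holds in conditional form. Followed literally, the article permits a superiority claim on either of two primary scores, each tested at two-sided 0.05. In that case the family-wise error is about 8–10%: 9.75% at correlation 0, falling to 8.4% at 0.7. The range rests on an assumed correlation and one test per score. If both scores must succeed, the error stays at or below 5% and there is no inflation. What is established is that the stated threshold does not hold 5% across the two primaries unless a rule is added, and that a split result has no agreed meaning in this document.

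**What to change.** Add one rule to the Primary outcome and Data analysis sections, chosen from:

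- **Fixed sequence:** one named score is tested at two-sided 0.05, and the other at 0.05 only if the first is significant. The order is the sponsor's choice; the order of the two bullets should not be taken as one.
- **Holm:** the smaller P-value is compared with 0.025 and, if significant, the larger with 0.05.
- **Both required:** superiority is claimed only if each score is significant at two-sided 0.05.

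If the full protocol or analysis plan already contains such a rule, the article's text should be brought into line with it.

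The rule must be fixed before the first-level unblinding described under Blinding, which discloses groups A and B before the analysis. With 330 and 110 patients planned, the group sizes alone would show which group is which. Trial status reports recruitment as on-going, so at the time of writing there was still room to do this.

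The cost is small. Under a fixed sequence the second score can be claimed only after the first. Holm costs some power through the 0.025 first step. Requiring both costs power by an amount that cannot be calculated from the article; it needs planning values for the two scores. None of the options needs new data or changes patient care.

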**Discussion:**

According to TCM theory, SQTX Granule has a regulating effect on abdominal pain, diarrhea and the syndrome of liver-spleen disharmony, which is similar to the symptoms of IBS-D. This study will provide objective evidence to evaluate the efficiency and safety of SQTX Granule in IBS-D treatment.

**Trial registration:**

ChiCTR-TRC-14004241.

Date of registration: 9 February 2014.

## Background

IBS refers to a clinical syndrome that presents as a common chronic gastrointestinal disorder. Patients suffer from abdominal pain or discomfort, bloating, and altered bowel habit, which vary in both degree and frequency, from slight to severe and from recurrent to persistent, respectively
[1]. The disease is one of the most common functional gastrointestinal (GI) disorders with a reported prevalence of approximately 5 to 20% worldwide
[1-3]. IBS is more commonly diagnosed in women than in men, and in patients younger than 50 years
[1,4,5]. IBS considerably reduces patients’ quality of life, interfering with their working ability and social activity, and it also results in a significant economic burden through decreased work productivity and increased healthcare costs
[6]. With the accelerated pace of life and changes in diet in recent years, neurological, psychiatric and infectious factors have caused an upward trend in the incidence of IBS
[7-9]. No biomarkers have been found for IBS diagnosis
[10], so IBS is diagnosed by assessing symptoms, according to the Rome III criteria
[11,12]. According to these criteria, four subtypes of IBS were recognised: IBS with constipation (IBS-C), IBS-D, mixed IBS (IBS-M), and unsubtyped IBS (IBS-U). Each IBS patient could switch from one subgroup to another over time. Current medication approaches for IBS are based on symptom reduction, yet many patients remain undertreated; meanwhile, many medication approaches are associated with side effects that result in less benefit to the patient, particularly in treatment for long-term relief of abdominal pain or discomfort.

Due to unsatisfactory treatment effectiveness, the search for and use of complementary and alternative medicines (CAM) has increased during the past several years around the world
[13-15]. Studies indicate an improvement both in the abdominal complaints and the quality of life in IBS patients adopting CAM treatment, which includes dietary supplements, TCM, acupuncture, moxibustion and botanicals
[13-16]. TCM is one of the most common CAMs used in China, and it has an over 5,000-year history of applications for various diseases, including IBS-D
[17]. According to TCM theory, one of the most important principles of diagnosis and treatment is symptom differentiation, which is based on four diagnostic methods (inspection, listening and smelling, inquiry and palpation) to collect clinical manifestations, including symptoms and TCM signs.

In IBS-D, the most common symptom type is liver-spleen disharmony, and it is primarily characterised by abdominal pain/discomfort, diarrhea, chest/flank/abdominal distension, belching, frequent sighing and emotion-related symptoms. According to the basic principles of TCM, IBS-D with liver-spleen disharmony is treated by relieving stagnation of liver *qi*, as well as improving the transportation function of the spleen. First recorded in the TCM classic ‘*Jingyue's Complete Works*’, *Tong-Xie-Yao-Fang* (TXYF) decoction has been applied since the Ming Dynasty (16^th^ century) to cure abdominal pain with diarrhea (liver-spleen disharmony). Modified from TXYF decoction, *Shun-Qi-Tong-Xie* (SQTX) Granule treats abdominal pain, distention and diarrhea in patients suffering from IBS-D (liver-spleen disharmony), and it is formulated with the Chinese herbs listed in Table 
1, which have all been approved by the China Food and Drug Administration (CFDA)
[18]. In preclinical trials and toxicological studies, no evidence of toxic effects has been found with SQTX Granule. Pharmacologic experiments showed that it has the effects of inducing spasmolysis, analgesia and reducing diarrhea in rats with diarrhea caused by stress. Phase II clinical trials also showed that SQTX Granule can improve symptoms of abdominal pain/discomfort and the degree and frequency of diarrhea for patients with IBS-D (liver-spleen disharmony).

**Table 1 T1:** **Standard formulation of ****
*Shun-Qi-Tong-Xie *
****(SQTX) Granule**

**Pinyin name**	**Latin name**
*Baishao*	*Paeonia lactiflora Pall.*
*Baizhu*	*Atractylodes macrocephala Koidz*.
*Xiebai*	*Allium macrostemon Bunge*.
*Cheqianzi*	*Hegba Plantaginis Asiaticae*
*Foshou*	*Citrus medica L. var. sarcodactylis Swingle*
*Boheyou*	*Oleum Mentha haplocalyx* Briq.

Chinese herbs have been used for a long time with good effects and few adverse events; however, a randomised, double-blind, placebo-controlled trial is still necessary to prove the efficacy and safety of any medication. As a phase III clinical trial, the objective of this study is to evaluate the efficacy and safety of SQTX Granule with a placebo in patients with IBS-D (liver-spleen disharmony). The results of this study will provide evidence regarding the value of SQTX Granule as an intervention for IBS-D.

## Methods/design

### Design

This study is designed as a randomised, double-blinded, placebo-controlled, multi-centre, superiority clinical trial. This study is a phase III clinical trial and has been authorised by the CFDA (Approval Number 2007 L02218). In addition, the study is registered with the Chinese Clinical Trial Registry (ChiCTR-TRC-14004241). The study is financially supported by Shaanxi Bosen Biological Pharmaceutical Group Co. Ltd, Xi’an, China. This funding source is providing test drugs, but it had no role in the design of this study and does not have any responsibility for analyses, interpretation of the data or the decision to submit results. Trained research nurses introduce the trial to patients, and give them information sheets and consent forms. All patients have to give their written informed consent prior to enrolment. The study’s flow chart is shown in Figure 
1.

**Figure 1 F1:**
[figure not shown]
**Study flow chart.** The flow chart of enrolment, allocation, intervention and assessment.

### Ethics

The trial protocol is conducted in accordance with the Good Clinical Practice Guidelines and the Declaration of Helsinki (2008)
[19]. Ethics approval has been obtained from the Clinical Trials and Biomedical Ethics Committee of West China Hospital of Sichuan University (Number TCM-2013-01). Written informed consent will be obtained from each patient.

### Recruitment

A total of 440 Chinese patients who fulfill the screening criteria will be recruited at eight large comprehensive hospitals in China: 1) West China Hospital of Sichuan University, 2) Affiliated Hospital of Chengdu University of TCM, 3) The First Affiliated Hospital of Heilongjiang University Of Chinese Medicine, 4) Affiliated Hospital of Jiangxi University of TCM, 5) Shanxi Provincial Hospital of TCM, 6) The First Affiliated Hospital of Guangxi University of Chinese Medicine, 7) Gansu Provincial Hospital of TCM and 8) Affiliated Hospital of Changchun University of Chinese Medicine. Each centre will recruit 55 patients through posters in local hospitals.

### Sample size calculation

According to the results of Phase II clinical trial, the response rates of SQTX Granule and placebo were 0.51 and 0.33, respectively. Assuming the response rates for TCM and placebo were 0.5 and 0.35, the sample size was calculated under the setting of alpha = 0.05 and beta = 0.80. Taking into account a drop-out of 15%, the sample size needs to be 150 cases for each group. A total of 440 patients will be recruited in this trial, including 330 cases for the SQTX Granule group and 110 cases for the placebo group in a 3:1 ratio.

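### The sample size statement is wrong as written: beta is mislabelled, 150 per group does not follow from the stated rates under the two-sided test, and 330:110 gives about 80% power only if nobody is lost

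*Protocol article*

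**What the plan says.** The Sample size calculation section of the protocol article first reports Phase II results: "the response rates of SQTX Granule and placebo were 0.51 and 0.33, respectively". It then sets more cautious design values ("Assuming the response rates for TCM and placebo were 0.5 and 0.35") and the error rates ("the sample size was calculated under the setting of alpha = 0.05 and beta = 0.80"). It does not say whether alpha is one- or two-sided. The stated result is "Taking into account a drop-out of 15%, the sample size needs to be 150 cases for each group". The next sentence fixes a total of 440, made up of "330 cases for the SQTX Granule group and 110 cases for the placebo group in a 3:1 ratio".

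The Data analysis section supplies the only sidedness in the document: "The statistical significance is defined as a two-sided" P-value below 0.05.

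The Primary outcome section lists the IBS-QOL and IBS-SSS scores. The response rate used for the sample size is not among the primary outcomes.

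**The concern.** Beta is the type II error probability, so the printed value would describe a trial with 20% power. Even with that label corrected, 150 per group after a 15% allowance looks too small for a difference of 0.15 around a mid-range response rate under a two-sided test. The figure is also expressed per equal group, while the trial randomises 3:1.

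This paragraph is the article's only justification of the trial's size. Someone interpreting a null result would take from it that 80% power was available with drop-out already covered. If the allowance is not delivered, the chance of missing a true difference of 0.15 in response rate is larger than stated.

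**Working it through.** **Inputs.** Rates 0.50 and 0.35, difference 0.15, drop-out 15%, arms 330 and 110 (all Sample size calculation); two-sided 0.05 (Data analysis); power 0.80, reading the printed beta as power. No continuity correction unless stated.

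**1. Beta taken literally.** With 20% power, a two-sided calculation needs about 27 to 28 per group before drop-out. That is nowhere near 150, so power of 0.80 must be meant.

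**2. The plan's figure, two-sided, 1:1.**
- Unpooled variance: n = (1.960 + 0.842)² × (0.50×0.50 + 0.35×0.65) / 0.15² = 7.849 × 0.4775 / 0.0225 = 166.6 per group.
- Pooled variance under the null (mean rate 0.425): n = [1.960×√(2×0.425×0.575) + 0.842×√0.4775]² / 0.0225 = 169.3 per group.
- After drop-out, dividing by 0.85: 196.0 and 199.2. Multiplying by 1.15 instead: 191.6 and 194.7.
- With continuity correction: 183 per group, or 211 to 216 after drop-out.

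None of these gives 150. The stated figure is below the evaluable number needed even before any drop-out.

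**3. What comes close to 150.**
- One-sided 0.05 at the stated rates: unpooled 131.2, giving 150.9 (×1.15) or 154.4 (÷0.85); pooled 133.2, giving 153.2 or 156.8. The range is 151 to 157.
- Two-sided 0.05 at the Phase II rates 0.51 and 0.33, with continuity correction: 127.7, and 127.7 / 0.85 = 150.2.

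Two different routes therefore lead to about 150, and neither uses the stated rates with the stated two-sided test.

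**4. What 330:110 delivers, two-sided, 0.50 against 0.35.**
- Equivalent 1:1 size: 2×330×110 / 440 = 165 per group; after 15% loss, 165 × 0.85 = 140.
- No loss, unpooled: SE = √(0.25/330 + 0.2275/110) = 0.05316; 0.15/0.05316 − 1.960 = 0.862; power 80.6%. Pooled: 78.8%.
- Full 15% loss (280.5 and 93.5), unpooled: SE = 0.05766; 0.15/0.05766 − 1.960 = 0.642; power 73.9%. Pooled: 71.8%. Exact enumeration of the chi-square test at 280/93 and 281/94 gives 71.6% and 71.9%.
- With a continuity-corrected test, exact power is lower: 75.4% at 330/110 and 67.1% at 280/93.

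**5. For comparison.** 150 per group with full 15% loss (127.5 each) has 68.0 to 68.8% two-sided power. A 3:1 trial with 80% power after 15% loss would need about 510 to 534 patients in total.

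**The case against.** Four points on the other side have force, and each limits what may be concluded.

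- **Sidedness.** A reader might infer that the size was calculated one-sided and contradicts the two-sided analysis. The sample size section names no sidedness, the one-sided match is only approximate, and the Phase II rates with continuity correction reach 150 as well. The Phase II route does not rescue the text, because the section says that 0.50 and 0.35 were assumed. It does mean that the origin of 150 is unknown.
- **Placebo arm.** A reader might infer that 110 on placebo falls 40 short of a required 150. A per-group number for equal allocation sets no minimum for one arm of a 3:1 design. By information, 330:110 equals 165 per group, which is more than 150:150. The defect is only that a 1:1 figure is quoted for a 3:1 trial.
- **Loss.** A reader might take 72-74% as the trial's power. The Data analysis section follows the intention-to-treat principle, with a full analysis set that needs one dose and one later observation. The section on withdrawal keeps the last data of patients who leave. Many early leavers would stay in the analysis, so 72-74% is the bound with full loss and the likely value lies between it and 79-81%.
- **Endpoint.** A reader might infer that the primary analysis is underpowered. The calculation concerns a response rate, whereas the primary outcomes are scores compared by ANOVA or a rank test. The documents give no effect size or standard deviation for those scores, so their power cannot be judged from this paragraph.

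At the Phase II rates, 330:110 would keep about 87-88% power even after full loss. The shortfall is measured against the plan's own, more cautious assumption, which is the relevant benchmark for what the plan claims.

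**Conclusion.** The statement needs correction, within those limits. The beta label is wrong. At the stated rates and the document's two-sided 0.05 level, the 1:1 requirement is about 167-170 evaluable per group (196-199 after 15% drop-out), so 150 does not reproduce. The actual 330:110 reaches about 80% power only with no loss, so the 15% allowance that the text says was made is not delivered under the two-sided test. If the full 15% were excluded, the type II risk for the response-rate comparison would be about 26-28% instead of 20%.

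This rests on reading the printed beta as power, on a test without continuity correction, on loss proportional in both arms, and on the difference of 0.15 holding among the patients analysed. It is a conclusion about the response rate only.

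**What to change.** Rewrite the sample size paragraph, with no change to recruitment or allocation:

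- Replace the beta setting with power = 0.80 (beta = 0.20).
- State that alpha = 0.05 is two-sided, in line with the Data analysis section.
- Remove 150 per group, or replace it with the two-sided 1:1 figure of about 196-200 after 15% drop-out.
- State that 330:110 gives about 79-81% power with no loss and about 72-74% if the full 15% are excluded from analysis, for response rates of 0.50 against 0.35, and name the test formula used.
- Say explicitly that this power concerns the response rate and not the primary IBS-QOL and IBS-SSS scores.

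The cost is one paragraph and a less favourable power statement. No patients are added and no analysis changes.
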